## Outcome Measures

### Primary Outcome Measure:

#### 1. Maternal sensitivity

Sensitive responses, that is the ability to respond appropriately to the child's attachment needs, has consistently been found to be the most reliable predictor of attachment security. The intervention, including The Circle of Security, has the aim to promote maternal sensitivity.

The measurement tool "Coding Interactive Behaviour" (CIB) will be used to code maternal sensitivity towards the child. Maternal sensitivity is observed during 5 minutes interaction (free play) between mother and infant.

CIB has good psychometric properties and has been validated in multiple longitudinal studies across cultures and across age groups (from newborn to adolescent). The system has previously been used for the purpose of research of the relation between a child and a mother with mental illness(es). Moreover, it has been used to evaluate the effectiveness of interventions.

[Time Frame: The mother-child relation will be videotaped and assessed during a home-visit by the health visitor after the intervention is finished when the child is around 9 months old.]

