The project will be conducted as a randomized controlled trial. The intervention group will receive a specific intervention and the control group will receive care as usual, in this context the standard treatment in antenatal care for vulnerable pregnant women and by the health visitor.

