## Study Design

Study Type: Interventional

Primary Purpose: Prevention

Study Phase: N/A

Interventional Study Model: Parallel Assignment

The study population will be stratified randomized on an individual level, thus half of the women, who agree to participate, is being randomized to the intervention group and the other half is being randomized to the control group. The trial participants will be allocated within each municipality to either control- or intervention group. The project personnel visiting the families to collect baseline data carry out the randomization. The project personnel bring a sealed envelope when visiting the families. In the envelope, the randomization group is stated together with a randomization number. The envelope is packed by a third party individual who receives a computer generated allocation list from another researcher. The envelopes get the numbers from this random sequence. The researcher generates the allocation list by block randomization with random

block sizes of 2. The random allocation list is generated once and will be destroyed after the sealed envelopes are packed.

Number of Arms: 2

Masking: Investigator, Outcomes Assessor

Allocation: Randomized

Enrollment: 100 [Anticipated]

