| Experimental: Intervention
The intervention consists of three key components aiming at promoting a better attachment between child and mother/parents and through that giving the child the best possible beginning of life. The three components aim at: 1) detecting ill-being in vulnerable pregnant woman and initiation of potential treatment, 2) strengthening knowledge sharing and organizing the course for the families across the sectors, 3) strengthening parenting skills. | Behavioral: Intervention
1) Detection of ill-being: An extended consultation with the midwife. The midwife will screen the women for symptoms of anxiety, depression and personality disorders. 2) Knowledge sharing: An additional midwife consultation accompanied by the health visitor. The aim of is sharing knowledge and transmission of information between the two sectors responsible for making a shared plan for the course of the process for the pregnant woman. 3) Strengthen parenting skills through: - Two visits by the health visitor before birth and eight after. The visits are based on the parent training program The Circle of Security, aiming at promoting a secure attachment between child and carer. - Teaching the woman/couple on the importance of breast-feeding and how to succeed. |

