[Time Frame: At birth]

16. Length at birth

Measurement documented in the birth record immediately after birth.

[Time Frame: At birth]

17. Head circumference at birth

Measurement documented in the birth record immediately after birth.

[Time Frame: At birth]

18. Maternal sensitivity

Sensitive responses, that is the ability to respond appropriately to the child's attachment needs, has consistently been found to be the most reliable predictor of attachment security. The intervention, including The Circle of Security, has the aim to promote maternal sensitivity.

The measurement tool "Coding Interactive Behaviour" (CIB) will be used to code maternal sensitivity towards the child. Maternal sensitivity is observed during 5 minutes interaction (free play) between mother and infant.

CIB has good psychometric properties and has been validated in multiple longitudinal studies across cultures and across age groups (from newborn to adolescent). The system has previously been used for the purpose of research of the relation between a child and a mother with mental illness(es). Moreover, it has been used to evaluate the effectiveness of interventions.

[Time Frame: The mother-child relation will be videotaped and assessed during a home-visit by the health visitor when the child is around 1 month.]

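### The protocol lists a masked outcomes assessor, but its wording for the primary outcome has the interaction assessed at a health visitor's home visit and names no separate masked coder

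*Protocol*

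**What the plan says.** All places are in the protocol.

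- **Study Design, masking entry:** "Masking: Investigator, Outcomes Assessor".
- **Outcome Measures, primary outcome 1 (maternal sensitivity), description:** CIB "will be used to code maternal sensitivity towards the child", from five minutes of free play. The person who codes is not named.
- **Same outcome, timing entry (child aged about nine months):** "The mother-child relation will be videotaped and assessed during a home-visit by the health visitor after the intervention is finished".
- **Outcome Measures, secondary outcome 18 (the same measure at one month), timing entry:** "The mother-child relation will be videotaped and assessed during a home-visit by the health visitor when the child is around 1 month".
- **Arms and Interventions, experimental arm:** the parenting component consists of "Two visits by the health visitor before birth and eight after", based on the Circle of Security programme. The knowledge-sharing component adds "An additional midwife consultation accompanied by the health visitor".
- **Study Description, design paragraph:** the control arm receives usual care, described as "the standard treatment in antenatal care for vulnerable pregnant women and by the health visitor".

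**The concern.** The primary outcome is a rating made by an observer, so the result depends on who rates and what that person knows. The masking entry promises a masked assessor. The time frame brings in a health visitor, and health visitors deliver the component of the intervention aimed at the very construct being rated: "The intervention, including The Circle of Security, has the aim to promote maternal sensitivity".

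Mothers and those who deliver the programme know the allocation, so masked scoring is the main protection for this endpoint. If the rater expects treated mothers to do better, that expectation is added to the difference between the arms. The planned regression with adjustment for baseline scores cannot separate it from a treatment effect. The one-month rating has the further difficulty that the postnatal visits may still be under way.

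**Working it through.** **Step 1. The passages side by side.**

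| Question | Answer in the protocol |
|---|---|
| Is the outcomes assessor masked? | Yes (Study Design) |
| Where is the interaction filmed and assessed? | At a home visit, with the health visitor named (primary outcome 1, secondary outcome 18) |
| Who delivers the parenting component? | Health visitors: 2 + 8 = 10 visits, intervention arm only (Arms and Interventions) |
| Do health visitors see control families? | Yes, as usual care (Study Description) |
| Who codes the CIB? | Not stated |
| Is the assessing health visitor different from the treating one? | Not stated |
| How is the assessor kept unaware of the arm? | Not stated |

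The first two rows agree only if the health visitor merely films, or if an assessing health visitor is kept unaware of the arm. The protocol states neither.

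**Step 2. What the assessor would know under the literal reading.**
- If she delivered the Circle of Security visits to the family, she knows the arm.
- If she gave the family usual care, she probably knows it.
- If she has had no contact with the family, nothing in the protocol shows that she knows it, and nothing shows that she does not.

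**Step 3. Size, as an illustration only.**

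Inputs from the protocol: enrolment 100, drop-out 20%, allocation in halves. The protocol's own figure reproduces: 100 × (1 − 0.20) = 80 completers, hence 40 per arm.

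Inputs that are assumptions: a two-sided 5% t-test, 80% power, and a rater shift b of 0.1 to 0.3 SD in favour of the intervention. The protocol gives none of these.

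With no true effect, the test statistic follows a noncentral t distribution with 40 + 40 − 2 = 78 degrees of freedom and noncentrality b × √(40/2) = 4.472 b. The critical value is 1.991.

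| Assumed shift b (SD) | Noncentrality | Probability of a significant result |
|---|---|---|
| 0 | 0 | 5.0% |
| 0.1 | 0.447 | 7.3% |
| 0.2 | 0.894 | 14.3% |
| 0.3 | 1.342 | 26.3% |

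A normal approximation gives 7.3%, 14.5% and 26.9%, so the choice of distribution hardly matters.

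For scale, the same calculation gives 80% power at a true difference of 0.634 SD. A shift of 0.2 SD is 0.2/0.634 = 32% of that, and 0.3 SD is 0.3/0.634 = 47%.

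**The case against.** The strongest reply is that the passages can be reconciled. The words naming the health visitor can attach to the home visit rather than to the assessing, and they stand in a time-frame field, whose purpose is to say when a measurement happens. CIB is a coding system, and a recording has little purpose if the score is given live. Filming at the visit followed by masked coding would fit the masking entry. Secondary outcome 18 repeats the same sentence, so it is not independent evidence for the literal reading. Stored videos would also allow masked re-scoring later, so even a live unmasked rating need not be final.

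Much of this stands. A reader might infer that the assessor knows the arm and that the primary outcome is in fact unmasked. The protocol does not establish either. It does not say that the visitor at nine months is the one who treated the family, and since health visitors also see control families, the profession alone does not reveal the arm. Nor do the figures above show that bias is present. They show what an assumed bias would do.

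What the reply does not remove is the wording. The text puts the assessing, as well as the filming, at the visit, and names no other assessor. A site that follows it literally would have the health visitor score the primary outcome. If masked video coding is intended, the time frame misdescribes the endpoint and still needs correcting. Nor is this a detail that can be left to an analysis plan: who scores the outcome is trial conduct, and the protocol already addresses it in two places that do not fit together.

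**Conclusion.** The point holds as a conflict within the protocol: a masked outcomes assessor is stated, but the wording for the primary outcome and its one-month counterpart does not secure it. This needs correcting before any scoring, because it concerns the only primary outcome and, taken literally, would allow ratings by someone who knows the allocation.

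The conflict rests on the protocol's text alone. The size does not: the false-positive rates of about 7%, 14% and 26% depend on assumed shifts of 0.1, 0.2 and 0.3 SD, an assumed two-sided 5% level and 40 completers per arm. The documents give no basis for choosing among those shifts.

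**What to change.** Reword the time frames of primary outcome 1 and secondary outcome 18 to say that:

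- the home visit only records the five minutes of free play, and the health visitor gives no rating;
- the CIB score used in the analysis is coded from pseudonymised video by the masked outcomes assessor already listed under Study Design, who has given no care to the family.

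The cost is new wording in two outcome entries, pseudonymised video files and a short delay between filming and scoring. The recordings and a masked assessor are already part of the plan.

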### Secondary Outcome Measure:

#### 2. Prenatal Parental Reflective Functioning Questionnaire

Measuring the mentalization skills or reflective functioning of the parents in relation to the unborn child.

[Time Frame: Baseline]

3. **Parental Reflective Functioning Questionnaire**  
Measuring the mentalization skills or reflective functioning of the parents in relation to the child, and refers to the capacity to treat the child as a psychological human. Consists of three sub scales, describing high, low or nor high neither low mentalization functioning in the parents.  
  
[Time Frame: Second follow-up:15 months after baseline (child 9 months old)]
4. **The Parenting Stress Index**  
Measuring stress in relation to parents and in relation to the child and dysfunctionality in the parent-child relationship. Questions are about the child's behavior, the parents' reactions and how the family functions.  
  
[Time Frame: Second follow-up:15 months after baseline (child 9 months old)]
5. **Edinburgh Postnatal Depression Scale**  
Measuring maternal depressive symptoms. The effectiveness of Edinburgh Postnatal Depression Scale (EPDS) for detection of depression at a clinical level is well-documented, and has been shown to have high sensitivity and specificity against a clinical psychiatric diagnosis of depression.  
  
[Time Frame: Baseline, first follow-up: 7 months after baseline (child 1 month old) and second follow-up:15 months after baseline (child 9 months old)]
6. **Maternal Antenatal Attachment Scale**  
Measuring maternal attachment to the unborn child, in terms of thoughts, feelings and behavior towards the unborn child. There are two dimensions: the quality of the attachment (emotional closeness/distance, positive/negative feelings, tenderness/irritation aimed at the unborn child) and intensity/time the mother is in attachment mode (how involved the woman is with the fetus)  
  
[Time Frame: Baseline]
7. **Warwick Edinburg Mental Well-being Scale**  
Measuring mental well-being in a broad understanding of the condition. Includes positive emotion, psychological function and interpersonal relations. All questions are formulated in positive phrases.  
  
[Time Frame: Baseline, first follow-up: 7 months after baseline (child 1 month old) and second follow-up:15 months after baseline (child 9 months old)]
8. **Ages and Stages Questionnaire - Social Emotional**  
Measuring the infant's socio-emotional development. The mother and father should complete the questionnaire and the responses are assessed separately. Includes self-regulation, compliance, communication, adaptive functioning, autonomy, emotions and interaction with other people.  
  
[Time Frame: Second follow-up:15 months after baseline (child 9 months old)]
9. **Experiences in Close Relationship - revised version**  
Measuring adults' attachment in close relationships. Measures 1) avoidant attachment style, characterized by fear of intimacy and interpersonal dependency and 2) fear of attachment, characterized by fear of being rejected and a craving for interpersonal closeness.  
  
[Time Frame: Baseline, first follow-up: 7 months after baseline (child 1 month old) and second follow-up:15 months after baseline (child 9 months old)]
10. **Family and Social Support Scale**  
Measuring parents perceived support from family, friends, society and their partner.  
  
The scale is used in many studies to measure the effect of social support on parents' health and well-being, family integrity, parents' perception of the child and the parent-child interaction.  
  
[Time Frame: First follow-up: 7 months after baseline (child 1 month old) and second follow-up:15 months after baseline (child 9 months old)]
11. **Adverse Childhood Experiences International Questionnaire**  
Measuring some of the most intense and frequently occurring causes of stress in the childhood, and the association between these causes and risk behavior later in life. Measuring family dysfunction, physical, sexual and emotional abuse and neglect of care from the parents (or other carers), different types of violence and witnessing of violence.  
  
[Time Frame: Second follow-up:15 months after baseline (child 9 months old)]
12. **Attitude towards breast-feeding**

The mothers and the fathers attitude towards breast-feeding before birth – scales to be selected

[Time Frame: Baseline]

13. Breast-feeding status

Self-reported breast-feeding status – scales to be selected

[Time Frame: First follow-up: 7 months after baseline (child 1 month old) and second follow-up: 15 months after baseline (child 9 months old)]

14. APGAR-score

Summarizing the health of the newborn child, including skin colour, breath, muscular tension, heartbeat and reflexes. Measured 1, 5 og 10 minutes after birth.

[Time Frame: At birth]

15. Birth weight

Measurement documented in the birth record immediately after birth.

[Time Frame: At birth]

16. Length at birth

Measurement documented in the birth record immediately after birth.

[Time Frame: At birth]

17. Head circumference at birth

Measurement documented in the birth record immediately after birth.

[Time Frame: At birth]

18. Maternal sensitivity

Sensitive responses, that is the ability to respond appropriately to the child's attachment needs, has consistently been found to be the most reliable predictor of attachment security. The intervention, including The Circle of Security, has the aim to promote maternal sensitivity.

The measurement tool "Coding Interactive Behaviour" (CIB) will be used to code maternal sensitivity towards the child. Maternal sensitivity is observed during 5 minutes interaction (free play) between mother and infant.

CIB has good psychometric properties and has been validated in multiple longitudinal studies across cultures and across age groups (from newborn to adolescent). The system has previously been used for the purpose of research of the relation between a child and a mother with mental illness(es). Moreover, it has been used to evaluate the effectiveness of interventions.

[Time Frame: The mother-child relation will be videotaped and assessed during a home-visit by the health visitor when the child is around 1 month.]

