## Study Description

**Brief Summary:** The aim of the project is to develop and evaluate an interdisciplinary and cross-sectorial intervention targeting pregnant women with psychosocial vulnerabilities. The objective is to 1) detect depression, anxiety and personality disorders in the pregnant women, 2) to increase knowledge sharing across the health care sectors and 3) strengthen the parents' parenting skills and thereby support a secure attachment between parents and child and thus promoting the child's well-being.

The overriding hypothesis is that an early multi-stringed, interdisciplinary and cross-sectorial intervention, with a long-term perspective from the early pregnancy throughout the child's first years of life, can effectively prevent disorders in the parent-child relation. The approach is to detect and treat depression and anxiety in the mother and strengthen the parents' parenting skills in families with maternal psychosocial vulnerabilities. The hypothesis indicates that the over-all intervention will result in improved interaction between child and parents which will make it possible to detect higher maternal sensitivity and a higher level of well-being among both children and parents in the intervention group compared to the control group.

The projects' specific hypotheses are;

- A systematic screening for anxiety, depression and personality disorders in the midwifery consultation will imply more pregnant women with symptoms of anxiety, depression and personality disorders being detected and offered treatment in the intervention group compared to the control group.
- Knowledge sharing across health care sectors will improve by the implementation of a joint consultation involving the vulnerable pregnant woman/families, the midwife and the health visitor and by a systematic transmission of information when the woman leaves the post-natal ward and is transferred to the health visitor.
- Parental skills in psychosocial vulnerable pregnant women and their partners can be strengthened by a parental training program and by education and dialogue about perceived challenges and breast-feeding. Parents in the intervention group will therefore gain greater knowledge on what it takes to make breast-feeding work successfully, be able to interact more appropriate with their children, and improve their mentalization skills and experience less stress compared to parents in the control group.

**Detailed Description:** Design, material and method:

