#### Data collection:

Data for evaluating the efficiency of the intervention are collected on three points of time; at baseline, after birth, when the child is aged four weeks, and at follow-up after the intervention has finished, when the child is around nine months. All data are collected in the homes of the families. To make an extra incentive to complete the questionnaires the participants receive a gift to the value of approx. 300 dk. kr. (approx. 45 USD) when completion of the follow-up questionnaire. Baseline data is collected for both control and intervention group before participants are familiar with the allocation of the randomization. The following paragraphs will describe the type of data that will be collected. Table 4 shows an overview of variables expected to be collected. Two different questionnaires will be developed specifically for the mother and for the father. The questionnaires look alike except that the mother's questionnaire contains questions on her attachment to the child in the belly and on her attitude and perception of breast feeding.

The questionnaires will be pilot tested by individuals from the target group to ensure that the questionnaires have a manageable size for participants and that questions are relevant. Afterwards the questionnaire will be revised accordingly.

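### Three secondary outcomes are measured only at baseline, before allocation is known, and a fourth records events that precede the trial; none of the four can show an intervention effect

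*Protocol*

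**What the plan says.** Under Secondary Outcome Measure the protocol numbers its outcomes 2 to 18. Three of them carry a baseline time frame ("Time Frame: Baseline") and no other:

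- Item 2, Prenatal Parental Reflective Functioning Questionnaire: "Measuring the mentalization skills or reflective functioning of the parents in relation to the unborn child".
- Item 6, Maternal Antenatal Attachment Scale: "Measuring maternal attachment to the unborn child, in terms of thoughts, feelings and behavior towards the unborn child".
- Item 12, Attitude towards breast-feeding: "The mothers and the fathers attitude towards breast-feeding before birth".

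Item 11, the Adverse Childhood Experiences questionnaire, is scheduled only at the second follow-up, when the child is nine months old. It is said to cover "causes of stress in the childhood, and the association between these causes and risk behavior later in life".

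On timing, the Data collection section states: "Baseline data is collected for both control and intervention group before participants are familiar with the allocation of the randomization". That section gives two later data points, four weeks after birth and about nine months after birth.

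On analysis, the Planned statistical methods section places primary and secondary endpoints alike under intention-to-treat. It assigns them to linear or logistic regression, adjusted for baseline scores where possible, and exempts no item.

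**The concern.** An outcome in a randomized comparison has to be something that allocation could have changed. A scale completed before the family learns its arm does not meet that condition, and neither does a record of events from before the trial. With these items on the outcome list, the plan as written compares the arms on quantities the programme cannot have moved. A nominally significant result could be read as an effect, and a null result says nothing about benefit.

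A related gap concerns the third specific hypothesis in the Study Description. It predicts that intervention parents will "gain greater knowledge on what it takes to make breast-feeding work successfully". Item 12 is the listed scale closest in subject, so it may be taken as the test of that prediction. It is completed before the intervention, and it measures attitude, not knowledge.

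**Working it through.** The protocol gives no figure on this point to reproduce. The check compares time frames and content, with one short illustrative calculation.

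**Step 1: order of events.** Under Study Design, the staff who visit to collect baseline data also carry out the randomization, and they bring a sealed envelope to the visit. Together with the Data collection statement, this puts baseline scores ahead of any knowledge of the arm.

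**Step 2: could items 2, 6 and 12 be measured later?** Both later data points fall after birth. Items 2 and 6 concern an unborn child, and item 12 is defined as an attitude before birth. As defined, none of them fits either follow-up visit.

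**Step 3: is a baseline-only time frame just shorthand for first measured at baseline?** No. Items 5, 7 and 9 list baseline and both follow-ups, so the protocol marks repetition where it intends it.

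**Step 4: does baseline adjustment rescue the analysis?** No. For items 2, 6 and 12 the baseline score is the outcome itself.

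**Step 5: item 11.** Its content is childhood adversity, including neglect by parents or carers, and the link with risk behaviour later in life. A nine-month-old has no later-life behaviour to report, so the parents' own childhood is the most plausible reading, although the protocol does not say so outright. Those events precede the trial. The score is collected after allocation, so arms could differ by chance, by differential reporting, or by differential drop-out. None of these is an effect on the exposure. If the stated 20% drop-out means no nine-month visit, 0.20 × 100 = 20 of the planned 100 women would have no score.

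**Step 6: count.**

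- Secondary outcomes: 18 − 2 + 1 = 17.
- Baseline only: items 2, 6 and 12, so 3/17 = 17.6%.
- With item 11: 4/17 = 23.5%.
- Remaining: 17 − 4 = 13 (items 3, 4, 5, 7, 8, 9, 10, 13, 14, 15, 16, 17 and 18). Each has at least one measurement after allocation.

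**Step 7: illustration for the three baseline-only items.** Assume one test per item at two-sided α = 0.05. The protocol states no α and says nothing about dependence between tests.

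- Independent tests: 1 − (1 − 0.05)^3 = 1 − 0.857 = 0.143, or 14.3%.
- Fully dependent tests (lower limit): 5%.
- Upper bound under any dependence: 3 × 0.05 = 15%.

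**Step 8: breast-feeding knowledge.** Item 12 is attitude at baseline. Item 13 is self-reported feeding status at one and nine months. No listed outcome measures knowledge after the intervention.

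**The case against.** The best defence is that collecting these instruments is sensible and the fault is one of labelling. The statistical section separates baseline from outcome scores in its descriptive plan and foresees adjustment for baseline, so the scales have a natural role as covariates. No sentence singles out a baseline-only scale for an arm comparison. This stands as an argument on severity. It does not remove the error, because the regression commitment covers all secondary outcomes and these items are on that list.

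Several stronger readings are tempting, and the documents do not support them:

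- **Item 11 has zero effect by construction, like the other three.** This is true of the past events but not of the measured score, which is taken at nine months and is open to differences in reporting and drop-out.
- **The false-positive risk is 1 − 0.95^4 = 18.5% over four items.** This needs an exact 5% null rate for item 11, which the previous point puts in doubt, as well as the unstated α and independence. Even 14.3% is only illustrative: items 2 and 6 both concern the relation to the unborn child, item 6 has two dimensions, and item 12 covers both parents.
- **The knowledge hypothesis fails because attitude is not measured again, so the scale should be repeated at one month.** Attitude is not knowledge, so a repeat would not test that hypothesis. With eight health-visitor visits planned after birth and the intervention ending before the nine-month follow-up, one month most likely falls during the programme. The protocol also refers to a table of variables that is not in the text at hand. The absence of a repeat is therefore established for the outcome list only.
- **The trial's main conclusion is at risk.** The primary outcome is observed maternal sensitivity at about nine months, which these items do not touch.

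**Conclusion.** The point holds and is a should-fix. Items 2, 6 and 12 cannot respond to treatment as scheduled, and any arm difference on them is chance imbalance. This rests on the sealed-envelope sequence being followed as described. Item 11 cannot show an intervention effect because it records earlier events, on the inference that the childhood in question is the parents'. A difference in its score would reflect chance, reporting or drop-out. The size is 4 of 17 secondary outcomes, of which 3 are baseline-only. The chance of at least one false positive on those three is about 14%, under assumptions that the protocol does not make.

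The knowledge part of the third hypothesis has no listed measure after the intervention, so item 12 cannot support a claim that it was tested. The primary outcome and the other 13 secondary outcomes are unaffected.

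**What to change.** 1. Move items 2, 6 and 12 from the secondary outcomes to baseline characteristics or covariates, and exclude them from between-arm testing. Item 2 could, for example, serve as the prenatal covariate for item 3, its postnatal counterpart.
2. Reclassify item 11 as a descriptive variable that is not tested as an outcome. State whose childhood it refers to, and note that collection at nine months limits its use as a moderator.
3. State that the prediction on breast-feeding knowledge is not tested by item 12, and that item 13 covers feeding status only.

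The cost is an edit to the outcome list and a sentence or two in the statistical section. No visit, instrument or participant burden is added and no data are lost. The secondary outcomes fall from 17 to 13.
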